## Abstract

**Background:**

Previous studies have shown that acupuncture is beneficial for the alleviation of chemotherapy-induced nausea and vomiting. However, there is a lack of clinical evidence concerning the effects of acupoint-matching on chemotherapy-induced nausea and vomiting.

**Methods/design:**

This is a parallel randomized controlled trial to evaluate the occurrence of nausea and vomiting after chemotherapy (the incidence of nausea and vomiting, frequency, VAS score, RINVR rating) as the main outcome for cancer. Quality of life, anxiety and depression scores are the secondary outcomes. Quality of life, anxiety and depression scores are the secondary phase. Use of remedy drugs, routine blood examination, and blood biochemical tests are the safety evaluation. We also compare the different effects of ST36 (single acupoint), CV12 (single acupoint), and ST36-CV12 matching groups.

**Discussion:**

The results of this trial are expected to explore the effects of matching different acupoints and to offer biologic plausibility for the use of acupuncture in the treatment of chemotherapy-induced nausea and vomiting (CINV).

**Trial registration:**

This trial is registered with clinicaltrials.gov NCT02195921, The date of registration was 17 July 2014.

**Electronic supplementary material:**

The online version of this article (doi:10.1186/s13063-017-2186-y) contains supplementary material, which is available to authorized users.

## Background

### Introduction

Vomiting and nauseas are common side effects of chemotherapy [1]. The management of these side effects is challenging because antiemetic drugs have adverse effects such as constipation [2]. Acupuncture, a non-pharmacologic therapy, may be helpful for patients to manage the side effects of chemotherapy [3]. It has been shown that acupuncture may reduce the side effects of chemotherapy such as vomiting, nausea, hot flashes, and fatigue [4–6]. Acupuncture treatment has been recommended since 1997 by the National Institutes of Health (NIH) to help patients undergoing chemotherapy deal with severe side effects like vomiting and nausea [7]. Electroacupuncture has been recommended on the basis of level 1 evidence for the prevention of chemotherapy-induced nausea and vomiting (CINV) [8]. Such evidence has displayed the efficacy of acupuncture; however, how to match the acupoints remains a problem for clinical treatment.

**Fig. 1 Fig1:**
[figure not shown]
The schedule of enrollment, interventions, and assessments

Acupoints are the material basis for acupuncture effects [9], and the matching of acupoints is key to enhancing the effects. For single acupoint use, Zusanli (ST36) is one of the best acupoints for treatment of stomach disease, as it is beneficial for regulating the qi flow and harmonizing the stomach [10]. Zusanli (ST36) and Zhongwan (CV12) are considered as the most effective matching acupoints for the stomach qi on the basis of He-sea and Front-mu acupoint-matching (ST36 is the lower He-sea point of the stomach and CV12 is the Front-mu acupoint of the stomach) [11].

This randomized controlled trial evaluates the effects of acupuncture on CINV after chemotherapy to offer biologic plausibility for addressing vomiting and nausea. We will conduct this trial using ST36 single, CV12 single, and ST36-CV12 matching to investigate the quality of life scores, and depression/anxiety score as a secondary objective for patients undergoing chemotherapy as well as to explore the matching rules of acupoints.

## Methods

### Participants

This trial will be carried out at the Tianjin Medical University Cancer Institute and Hospital. All participants included in this trial are from the wards of integrated Chinese and western medicine, galactophore, lymphoma, and radiology.

### Study design

Random parallel control will be used as the clinical test design. Participants are randomly assigned to treatment groups: the ST36 single group (distal), CV12 single group (local), ST36-CV12 matching group (proximal-distal), and control group.

### Inclusion criteria

Inpatients from Tianjin Medical University Cancer Hospital who meet the following requirements will be eligible for enrollment: (1) diagnosed with cancer by imaging, cytology, pathology, and requiring chemotherapy; (2) Karnofsky (KPS) score ≥70 points; can take care of themselves; (3) no gender criteria, aged between 18 to 80; (4) inpatient or outpatient; (5) can be receiving single or multiple rounds of chemotherapy, but each patient should only be included once; (6) cancer patients undergoing chemotherapy combined with cisplatin (cisplatin ≥75 mg/m^2^) or anthracycline therapy (doxorubicin ≥40 mg/m^2^ or epirubicin ≥60 mg/m^2^); (7) expected lifespan longer than 6 months; (8) providing a signed hard copy of the agreement form.

### Exclusion criteria

Participants with any of the following conditions will be excluded: (1) radiotherapy and chemotherapy used at the same time; (2) nausea and vomiting due to cancers of the digestive system, such as gastric cancer; (3) chemotherapy patients with serious complications or severe liver/kidney function abnormalities [glutamic oxaloacetic transaminase (AST), glutamic-pyruvic transaminase (ALT), total bilirubin (TBIL) triple normal levels, blood urea nitrogen (BUN) and urine creatinine (Cr) double normal levels]; (4) fitted with pacemakers or other implanted medical electronic devices; (5) needle site with inflammation, scarring or trauma, or other serious systemic infection; (6) long-term use of opioids or metabolic imbalance (electrolyte imbalance) which cause vomiting; (7) a history of mental illness, language communication disorders; (8) postoperative patients with gastrointestinal obstruction and other mechanical risk factors; (9) patients with brain metastases or symptoms of increased intracranial pressure; (10) pregnancy or breast feeding.

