### Outcomes

#### Primary outcome

The evaluation of nausea and vomiting is classified by the incidence of nausea and vomiting. In this trial, we use the Rhodes Index of Nausea, Vomiting and Retching [15] to score the incidence of nausea and vomiting. It could also be used to evaluate the duration, frequency, and severity of nausea and vomiting.

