### Participant timeline

The enrollment will be carried out before the first day of chemotherapy on day 0. The electroacupuncture intervention will be given once daily from day 1 to day 4. All assessments will be scheduled from day 0 to day 5 (Fig. 1)

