### Statistical analysis

Statistical analysis will be conducted using SPSS (v.22; IBM Corp, Armonk, NY, USA). We will express normally distributed continuous outcomes using mean (SD) and skewed data with median (range). Dichotomous outcomes will be expressed as frequency or incidence. If the data are normally distributed, we will use ANOVA with Bonferroni-corrected pair-wise comparisons to compare the primary outcomes among the four treatment groups. If the data are not normally distributed, we will use a Kruskal-Wallis test to compare the four treatment groups and a Wilcoxon rank-sum test for the pair-wise comparison for the primary outcome. Intergroup differences in categorical data (Common Terminology Criteria for Adverse Events) will be assessed using the chi^2^ test or Fisher exact tests (two-tailed), as appropriate. Repeated measures analysis of variance (R-ANOVA) will be used to assess the frequency of vomiting, and the Visual Analogue Scale for nausea and nausea and vomiting and retching among the four study groups. Length of no days of nausea and vomiting will be calculated using Kaplan-Meier analysis and compared among the groups using the log-rank test. Subgroup analysis based on single or multiple chemotherapy sessions will be performed to compare the efficacy of basic antiemetic regimens plus electroacupuncture or an antiemetic regimen only on inducing a complete response. A *p* value <0.05 will be considered to be statistically significant.

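### Patients already nauseated or vomiting on day 0 can enter and be counted in the incidence and symptom-free-time outcomes, which dilutes those two comparisons

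*Protocol article*

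**What the plan says.** Four of the ten exclusion criteria bear on vomiting, and each is framed by a cause:

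- (2) "nausea and vomiting due to cancers of the digestive system, such as gastric cancer"
- (6) "long-term use of opioids or metabolic imbalance (electrolyte imbalance) which cause vomiting"
- (8) "postoperative patients with gastrointestinal obstruction and other mechanical risk factors"
- (9) "patients with brain metastases or symptoms of increased intracranial pressure"

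Inclusion criterion (5) says that patients "can be receiving single or multiple rounds of chemotherapy, but each patient should only be included once". It states no symptom-free interval since the previous round.

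Under Primary outcome, "The evaluation of nausea and vomiting is classified by the incidence of nausea and vomiting", with no limit to new onset. The abstract describes the main outcome as occurrence after chemotherapy. Under Statistical analysis, "Length of no days of nausea and vomiting will be calculated using Kaplan-Meier analysis", and groups are compared by the log-rank test. That section contains no baseline term and no rule for symptoms present at entry.

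The Participant timeline puts enrolment on day 0, before chemotherapy starts, and places all assessments between day 0 and day 5. Fig. 1 is not available here, so it cannot be seen which instruments are used on day 0.

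**The concern.** The criteria aim to isolate emesis caused by chemotherapy, but they do so only by attribution. A patient in a later round who still has nausea from the previous one, or who has anticipatory nausea, has none of the listed causes and meets every criterion.

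For a binary incidence outcome, such a patient may be counted as an event under any treatment. For time free of symptoms, such a patient has little or nothing to prolong. Both comparisons then partly measure a state that existed before randomisation, incidence is raised in every arm, and the contrast between arms narrows. The incidence itself also becomes harder to read as chemotherapy-induced.

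Exclusion (2) adds an ambiguity. It can be read as removing all patients with digestive-system cancer, or only those with symptoms at screening.

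**Working it through.** **Inputs.** From the Sample size calculation: 40 patients per arm; adjusted significance level 0.05/6 = 0.0083, two-sided; mean (SD) 1.18 (0.53) for CV12 and 1.82 (0.69) for control; stated minimum 27 per arm at 90% power. Assumed, because the article gives no figure: the share b symptomatic on day 0 (10%, 20%, 30%), and incidences in symptom-free patients of 60% (control) and 40% (electroacupuncture).

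**1. The plan's own figure.** The difference is 1.82 - 1.18 = 0.64, and the root-mean-square SD is sqrt((0.53² + 0.69²)/2) = 0.615. The normal approximation gives 29 per arm (28 with the average SD of 0.61), close to the stated 27. The exact t calculation gives 31 (30 with SD 0.61). At 40 per arm, power is 97%. This sizing concerns a mean score, not incidence, and the point does not depend on it.

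**2. Incidence.** Suppose every patient symptomatic on day 0 is an event in every arm. Observed incidence in an arm is then b + (1 - b)p, and the difference between arms is (1 - b)(p_control - p_EA).

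| b | Control | Electroacupuncture | Difference |
|---|---|---|---|
| 0 | 60% | 40% | 20 points |
| 10% | 64% | 46% | 18 points |
| 20% | 68% | 52% | 16 points |
| 30% | 72% | 58% | 14 points |

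**3. Does restricting to symptom-free patients help, given the smaller set?** The set per arm is 40(1 - b) = 36, 32 or 28. Take b = 20% and a critical value of 2.638 for alpha 0.0083.

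- All randomised: SE = sqrt((0.68×0.32 + 0.52×0.48)/40) = 0.108; 0.16/0.108 - 2.638 = -1.16; power about 12%.
- Symptom-free only: SE = sqrt((0.60×0.40 + 0.40×0.60)/32) = 0.122; 0.20/0.122 - 2.638 = -1.00; power about 16%.

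With a pooled variance under the null hypothesis, the second figure is about 14% and the first is unchanged. The gain is modest, but restriction does not lose power under these assumptions. Both figures are low because the trial was not sized on incidence.

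**4. Mean score, as a pessimistic case.** If symptomatic patients had no treatment effect at all and the SD stayed at 0.615, the 0.64 difference would become 0.576, 0.512 and 0.448 at b = 10%, 20% and 30%. Power at 40 per arm would be 93%, 84% and 71%. Nothing in the article says these patients cannot improve on a score, so this is an outer illustration and not an estimate.

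**5. Chance imbalance.** The difference between two arms in the share symptomatic on day 0 has standard deviation sqrt(2b(1 - b)/40). At b = 20% this is sqrt(0.008) = 0.089, or about 9 percentage points. It is random in direction.

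**The case against.** The case on the other side is substantial, and much of it stands.

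- **Bias.** A reader might infer that symptomatic entrants favour one arm. Allocation is central and 1:1:1:1, so they are balanced in expectation. What remains is dilution and chance imbalance.
- **Every contrast.** A reader might infer that all outcomes are diluted and that no covariate can help. The trial is sized on a mean vomiting score, and the primary comparison is by ANOVA or a rank test. A patient with symptoms at entry can still score lower under electroacupuncture, and a day-0 score can be adjusted for. The sample-size text mentions change scores, which implies a baseline, although the Statistical analysis section does not take this up. Covariate choice may also be left to an analysis plan that is not shown.
- **Event at time zero.** Nothing in the article says that day-0 symptoms are themselves events, or that the Kaplan-Meier clock starts on day 0. A patient nauseated on day 0 may have none afterwards. The factor (1 - b) applies in full only if all such patients remain events in every arm.
- **Exclusion (2).** It might be called unworkable. Read as a condition present at screening, it can be applied. The fault is that the article does not say which reading is meant.
- **Breadth.** Admitting later rounds is deliberate, and a subgroup by single or multiple sessions is planned. That subgroup does not identify who was symptomatic on day 0.

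The gap itself is not answered. The article prints both eligibility lists in numbered form, and no other section deals with symptoms at entry.

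**Conclusion.** The point holds for incidence and for the Kaplan-Meier outcome. The stated criteria admit patients already symptomatic on day 0, and the stated analysis does not separate them. The consequence is reduced sensitivity, not a directional error. On the assumed 60% and 40% incidences, and with all such patients remaining events, the 20-point difference falls to 18, 16 and 14 points at b = 10%, 20% and 30%. The value of b is unknown and may be small, and if some of these patients have no symptoms after chemotherapy, or respond to treatment, the loss is less. For mean scores the effect differs in kind and can be handled by adjusting for the day-0 score.

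**What to change.** 1. Record nausea, vomiting and retching for every patient on day 0, before allocation. Assessments already start on day 0, so this needs at most a clarification of what is measured then.
2. Run the incidence and Kaplan-Meier analyses in patients symptom-free on day 0, and report the all-randomised analysis alongside. Because the subset is fixed before allocation, the randomised comparison is preserved. State the definition of symptom-free, and which analysis leads, before any unblinded data are seen.
3. Include the day-0 score as a covariate in the score analyses.
4. State whether exclusion (2) removes all digestive-system cancers or only those with symptoms at screening.

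The cost is a smaller set for two analyses: 36, 32 or 28 per arm at b = 10%, 20% or 30%. Those results also apply to a narrower population. Recruitment need not change.

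An entry criterion on symptoms before chemotherapy is optional. The trial is already recruiting, so a change now would mix two populations and add screen failures among later-round patients. If one is added, it should not rest on antiemetic use: the Control group section does not say when dexamethasone starts, and such a criterion could overlap with study prophylaxis.

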### Safety

Routine blood tests, liver/kidney function, constipation, diarrhea, and other antiemetic side effects, or adverse reactions will be assessed.

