## Abbreviations

ALT: Glutamic-pyruvic transaminase
AST: Glutamic oxaloacetic transaminase
BUN: Blood urea nitrogen
CINV: Chemotherapy-induced nausea and vomiting
Cr: Urine creatinine
CRF: Case report form
CV12: The Zhongwan acupoint
FACT-G: Functional Assessment of Cancer Therapy - General
KPS: Karnofsky score
NIH: National Institutes of Health
ST36: The Zusanli acupoint
TBIL: Total bilirubin

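### The creatinine part of exclusion (3) names a urine measure, which does not rise as kidney function falls and does not match the blood tests named elsewhere; whether it and BUN are joint or alternative conditions is left open

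*Protocol article*

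**What the plan says.** In the protocol article (Methods, Exclusion criteria), item (3) removes "chemotherapy patients with serious complications or severe liver/kidney function abnormalities". A bracket then gives limits: three times normal for AST, ALT and total bilirubin, and for the kidney "blood urea nitrogen (BUN) and urine creatinine (Cr) double normal levels". The abbreviation list carries the same definition, "Cr: Urine creatinine".

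Laboratory tests are named in two other places. The abstract (Methods/design) says that "routine blood examination, and blood biochemical tests are the safety evaluation". The Safety section lists "Routine blood tests, liver/kidney function" before the clinical side effects. Neither place mentions a urine sample, and neither lists the kidney analytes.

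Inclusion criterion (6) admits patients receiving cisplatin at 75 mg/m² or more, alongside patients on anthracyclines. Exclusion criterion (6) separately removes patients whose vomiting comes from metabolic imbalance.

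**The concern.** An upper limit screens for organ failure only if the quantity goes up as the organ fails. BUN does this for the kidney. Urine creatinine does not. The criterion therefore pairs one informative analyte with one that carries no signal in the direction the limit looks.

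Two further points follow from the text. First, the urine specimen stands alone: the other analytes in the bracket are ordinarily measured in blood, and the tests named elsewhere are blood tests or kidney function with no specimen stated. Second, the word joining BUN to creatinine does not say whether one doubled value excludes a patient or whether both are needed, and the effect of the faulty part depends on that.

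What is at stake is eligibility. Some enrolled patients receive cisplatin, so renal screening has a safety purpose. The primary outcome is nausea and vomiting, which impaired kidney function may itself cause, so patients who slip through could add symptoms not due to chemotherapy. Staff who apply the printed specimen and staff who assume a blood value would also screen differently.

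**Working it through.** The documents state no figure on this point, so there is nothing to reproduce. The check sets the sections side by side and then asks what each reading of the rule does.

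**Specimen, by section**

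| Place in the protocol article | What it names |
|---|---|
| Exclusion criteria, item (3) | BUN and urine creatinine, each at double normal |
| Abbreviations | Cr defined as urine creatinine |
| Abstract, Methods/design | Routine blood examination and blood biochemistry |
| Safety | Routine blood tests, and liver and kidney function with no specimen or analyte given |

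The first two agree with each other. They do not fit the third, and the fourth does not resolve the matter.

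**Behaviour of the two creatinine measures.** This is a simple mass balance and an assumption of this review; the documents do not discuss it. Let P be daily creatinine production, G the filtration rate and B the blood level. Tubular secretion and other losses are ignored.

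- Excretion in urine = G × B. At steady state this equals P, so B = P / G.
- If G falls to G/2, the new steady state is B = P / (G/2) = 2P/G. The blood level doubles.
- Urinary excretion is then (G/2) × (2P/G) = P, a change of 0%.
- Just after the fall, before B has risen, excretion is (G/2) × (P/G) = P/2. It moves down, not up.
- A spot urine concentration is P/V, where V is urine volume. With P fixed it doubles if V halves, so concentrated urine in a person with sound kidneys can double it.

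The phrase double normal is read here as at or above twice the normal level. On that reading a loss of filtration that doubles the blood value does not bring the urine value to its limit.

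**What the rule does under each reading.** Let s be the share of patients with severe renal impairment whose BUN meets its limit, and q the chance that urine creatinine meets its limit. The documents give neither. Treat q as unrelated to renal impairment and to BUN, in line with the mass balance.

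| Reading | Impaired patients excluded by the bracket | As q approaches 0 | Patients with normal BUN wrongly excluded |
|---|---|---|---|
| Either value suffices | s + q − sq | s | q |
| Both values required | s × q | 0 | 0 |

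Under the first reading BUN does all the useful work and the creatinine part adds only chance exclusions. Under the second it blocks the BUN part. The creatinine part contributes nothing useful under either, but the damage to the whole rule differs greatly. The two harms also belong to different readings: the healthy patient with concentrated urine is excluded only under the first, and the general failure of the rule arises only under the second.

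**The case against.** A reader might infer that the renal exclusion as a whole cannot work, or removes almost nobody. The documents do not support that. BUN has its own double-normal limit, and the governing words cover "severe liver/kidney function abnormalities" in general, so an investigator can exclude a patient without using creatinine. Near-total failure of the bracket needs the joint reading, which is arguably the less natural one. The bracket is a compressed list in which the conjunction may simply link analytes that share a multiple; the same logic would require AST, ALT and bilirubin all to be tripled before the liver part applied. This objection stands, and it limits the point to one part of the rule.

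A reader might also infer that creatinine is absent from the trial's blood panel. That is not shown. A urine measure cannot be part of a blood test, but the article does not list the panel's analytes, and the sections cited describe safety evaluation rather than screening. A condensed article need not give that list. By the same token, the article does not show that blood creatinine is measured.

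The wording may be a labelling or translation slip for a blood measure, and the abbreviation list may merely copy it. That is plausible but cannot be confirmed from the document. A slip in an operative eligibility limit still needs correcting, because nothing else in the article corrects it.

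Finally, the consequences are not quantified: no prevalence of renal impairment is given. Exclusion criterion (6) catches some metabolic vomiting independently. With 1:1:1:1 randomization any remaining renal nausea should fall on all arms alike, adding noise rather than systematic bias. That also stands, and it bears on severity.

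**Conclusion.** The point holds for the creatinine part of exclusion (3). It names a specimen that is uninformative in the direction of the limit and does not fit the blood tests named elsewhere, so it cannot contribute to identifying severe renal impairment. This rests on the mass balance above and on reading the limit as an upper one.

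The wider claim that the renal rule fails is not established. BUN and the general wording still screen some patients, and the rule would largely fail only if both values must be doubled, which the text leaves open.

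Severity is minor to moderate. The number of patients affected cannot be estimated from the document. Sample size, power, alpha and the comparability of the arms are untouched. The reason to act is that the criterion governs who enters a trial that includes cisplatin-treated patients, and two staff members could apply it differently.

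**What to change.** Reconcile the creatinine specimen in the Exclusion criteria and in the abbreviation list with the blood biochemistry in the abstract and the kidney function tests in the Safety section, so that all four places refer to the same measure. In the same line, state whether BUN and creatinine are alternative or joint conditions. The multiple of normal and the clinical rule remain the sponsor's to decide. If a urine measure is truly intended, the text should say how it is collected and in which direction an abnormal value counts.

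The cost is a one-line correction to the protocol and the case report form, with possibly a few more screen failures. It needs no new test if creatinine is already measured in the blood biochemistry, but that is an assumption. No statistical section needs to change. If patients have already been screened, it is worth recording which creatinine measure was used.
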